## Abstract

**Introduction:**

A strong body of evidence exists relating to inequality in general healthcare experience and outcomes for children and young people with learning disabilities and/or who are autistic compared to those without. Healthcare practitioners describe feeling less capable and confident to deliver care to children with learning disabilities, as well as having less capacity. However, there is little research specifically in cancer care that explores access and acceptability of provision for children with learning disabilities and/or those who are autistic. This is despite some cancers being more prevalent in syndromes associated with learning disabilities, for example Down’s Syndrome. We aim to explore the needs and experiences of children with/without learning disabilities and/or who are autistic and their families receiving cancer care. This inclusive study will provide evidence of whether, and what, inequity exists, for whom and why, generating evidence of what issues affect all children and young people receiving cancer care and what are particular to those with learning disabilities and/or who are autistic.

**Methods and analysis:**

We will use a transformative mixed methods design, comprising an individual staff and organisational level survey, retrospective case note review, ethnographic observations of clinical care, family and staff interviews, and participatory workshops. The ethnographer will follow and observe individual children and their families. We will use a ‘toolbox’ of creative participatory methods, including providing a co-designed research data collection journal to support elicitation of the child’s perspective. Data will be analysed using thematic analysis. The study will run from January 2025 to January 2026. The project is registered on ClinicalTrials.gov (Identifier: NCT06481527). Health Research Authority approval has been granted (REC Reference no. 24/LO/0410 | IRAS Project ID: 335623).

**Discussion:**

The mixed methods approach using survey and qualitative design will support a broad scope and in-depth understanding of the barriers and facilitators to inform equitable cancer care delivery for children with and without learning disabilities and/or who are autistic. Potential limitations are acknowledged. For example, resource constraints mean that the focus of the ethnography work package is within two hospital sites, which may limit broader comparisons and thematic development. Dissemination of findings will include papers specific to each work package. Recommendations for clinical practice will be developed, including staff training, healthcare planning and innovative solutions for improving the cancer care experience. These outputs will directly inform quality improvement from a local to national and international context in cancer care around children and young people with learning disabilities and/or who are autistic.

## Introduction

There is a long history of adults with learning disabilities experiencing poor treatment, care and discrimination in hospital. In 2007, for example, Mencap, a United Kingdom [UK] charity, published “Death by indifference” drawing attention to the cases of six people with learning disabilities who died unnecessarily in hospital and calling on the government to take “serious action” [1]. More recently evidence has shown that aspects of hospital care are also inequitable for children with learning disabilities, comparative to children and young people without learning disabilities, with staff reporting feeling less capable and confident to deliver care to those with learning disabilities, as well as having less capacity [2]. Similarly, a recent survey in the USA highlighted that children who are autistic are four times more likely to have unmet healthcare needs, when compared to children without disabilities, which was also higher than for children with other disabilities [3].

In relation to cancer care, there is limited research that explores access and acceptability of provision for underserved populations, such as children with learning disabilities and/or who are autistic. Recent work in adults with disabilities emphasises a lack of attitudinal and institutional preparation regarding cancer from healthcare professionals and institutions [4,5]. However, much less is known about how this inequality manifests with regards to experience and outcomes in paediatric cancer care [6]. Moreover, there is no known research that specifically seeks to understand the needs of children with learning disabilities and/or who are autistic, who also have cancer, and their families, so that services can be delivered equitably. This is despite the fact that certain cancer typologies are more prevalent for children and young people with learning disabilities compared to those without learning disabilities (Age 0–9: 0.7% vs. 0.1%; Age 10–17: 0.4% vs. 0.1%) [7]. For example, children and young people with Down’s Syndrome have greater risk of leukaemia [8] and poorer treatment outcomes [9,10] compared to children and young people without learning disabilities, including significant differences in treatment response and toxicity profiles. For other rare syndromes, such as Trisomy 13 and 18, population level data is limited but there is a similar pattern of an uneven distribution of certain cancer typologies [11,12]. Similarly, genetic pre-dispositions of different cancer profiles have been identified that are associated with diagnoses of Autism Spectrum Disorder (ASD) and other neurodevelopmental conditions [13–16], although globally incidence is equal between those who are autistic and those who are not. However, cancer mortality risk for those who are autistic is estimated to be nearly double compared to those who are not autistic, in a young adult population [17]. This difference arguably is related “to disparities in optimal cancer care” for reasons of limited screening access, delayed diagnosis and ineffective therapy for those patients who are also autistic [6]. Similar findings have been reported in adults with learning disabilities [18].

Children and young people with cancer who do not have learning disabilities and who are not autistic, report varying experiences of care and treatment. Their journey’s to cancer diagnosis are often protracted based on numerous factors, including clinicians overlooking signs and symptoms associated with possible diagnosis because of its rarity in this cohort [19], with reports of parents feeling they are not being listened too and sometimes having to engage in disputes and demand investigations [20]. When receiving cancer care, children and young people emphasise the importance of familiar environments, emotional support, and being informed about their treatment [21]. Older children in particular value involvement within interactions with clinicians and autonomy around decision-making, while younger children rely on their parents to greater extent [20–23]. How applicable such findings are to children and young people with learning disabilities or who are autistic is not known.

There are many complications of systemic anti-cancer treatment, which reduce quality of life: including nausea and vomiting; mucositis; constipation and diarrhoea; anaemia; anorexia; hair loss and febrile neutropenia [24,25]. Specific chemotherapy agents can cause particular morbidities, for example neuropathic pain from the use of vincristine [26]. Targeted treatments including surgery and radiotherapy can also have complications, such as radiation dermatitis [25]. We do know that one of the particular challenges faced in treating children with Down’s Syndrome and Leukaemia is balancing curative therapy against potential toxicities, requiring increased used of supportive care [8]. For example, chemotherapy tends not to be tolerated very well with a greater risk of side effects, particularly serious infections, which can make treatment more challenging [8]. Survival is also impacted. While Acute Myeloid Leukaemia in children with Down’s Syndrome is extremely sensitive to the effects of chemotherapy and responds very well to treatment, with trials suggesting a 5-year overall survival of more than 90%, this is not the same for Acute Lymphoblastic Leukaemia, where survival is lower than in the wider population [9,10]. Study based evidence for children who are autistic is less well developed. Nevertheless, we can anticipate challenges associated with some of the physical manifestations which overlap with common cancer or cancer treatment-related symptoms such as pain, sleep disturbances and fatigue, gastrointestinal (GI) problems or immune dysregulation [7]. These symptoms can be exacerbated by cancer-directed therapy or be misinterpreted. Furthermore, difficulties in communication in patients who are autistic can be an additional challenge to fully understanding their experience.

In addition to having intellectual impairment, children with learning disabilities may also have sensory and physical impairments adversely affecting speech, feeding and mobility [26]. They are almost twice as likely to report three or more health problems and more than four times as likely to suffer from a psychiatric disorder than children without learning disabilities [27]. Like some children who are autistic, their ability to understand information about hospital care and treatment may be severely limited, they may not be able to communicate their needs verbally, and may need additional support with all aspects of hospital life [28]. Those with challenging behaviour will find it particularly difficult, especially if care is not delivered in a therapeutic environment [29]. How these added complexities impact on the delivery of cancer care is unknown. The National Children’s Bureau [30] refer to children with learning disabilities as “an invisible group in society”, arguing that, “the more complex their needs, the more invisible they appear to become”, and as such those who also have cancer are at risk being doubly excluded.

This project seeks to build on previous work in which parents and children have shared experiences of discriminatory practices and of diagnostic overshadowing while asserting that they have not been properly listened to [28–30]. Within the field of paediatric cancer care, this project aims to address these research gaps and support implementation of ‘The learning disability improvement standards for NHS trusts’ [31,32], which encompasses: Respecting and protecting rights; Inclusion and engagement; Workforce; and Specialist learning disability service provision.

This evidence is needed to understand the context for making reasonable adjustments according to specific intellectual, emotional, social and physical needs. As personalised medicine is gaining popularity, we need a better understanding of what treatment outcomes matter to patients and families, particularly those with learning disabilities and/or who are autistic, for whom organisations have a legal responsibility to deliver reasonably adjusted care [33,34].

## Aim

Our aim is to understand the determinants of equitable cancer care for children and young people from diagnosis through to survivorship or palliative care, generating evidence of what issues affect all children and young people receiving cancer care and what are particular to those with learning disabilities and/or who are autistic.

## Objectives

### Phase 1 objectives

a. To compare healthcare professionals’ perceptions of their **capacity, capability and confidence** to deliver safe, holistic, individualised cancer care to children and young people with and without learning disabilities and/or autism

*We hypothesise that health professionals will perceive that they have less capacity, capability and confidence to deliver safe, holistic, individualised cancer care to those with learning disabilities and/or who are autistic and their families, compared to those without.*

b. To compare patient demographics, **care trajectory, symptom profiles and clinical** outcomes related to cancer care for children and young people with and without learning disabilities and/or autism

*We hypothesise that* c*hildren with learning disabilities and/or who are autistic*

- *will have a longer length of stay compared to children without learning disabilities and/or who are autistic and their families*- *will have increased number and severity of side effects compared to children without learning disabilities and/or who are autistic and their families*

### Phase 2 objectives

a. To compare the needs and experiences of holistic, individualised cancer care and what outcomes matter mostb. To understand what constitutes a **safe and therapeutic environment** for the delivery of holistic, individualised cancer care to children and young people with and without learning disabilities and/or who are autisticc. To understand the process of **transitioning from child to adolescent, and adolescent to adult healthcare** for children and young people with and without learning disabilities and/or who are autistic

### Phase 3 objectives

a. To identify and prioritise potential **innovative solutions** for improving experiences of cancer careb. To co-design an open access **repository of information resources**

We anticipate that findings will enable healthcare professionals make better clinical decisions, helping to ensure that resources and interventions promoting equity are targeted to those who need them, how and when they need them. Furthermore, that the findings will be a catalyst for multiple improvements via increasing awareness, targeted training and further development of tailored interventions relevant to cancer care (Box 1).

Box 1: Proposed targets for improvementUnmet needsAdverse health outcomes/long-term emotional damage to children from poor practiceNumbers and type of complaints/clinical incidentsPatient/parent satisfaction and experience of careStaff capability/confidenceParental trust/confidence in careTimely dischargeFinancial cost to NHS/familiesTherapeutic environment for delivery of cancer careTransition experience from child to adolescent, or adolescent to adult services

Terminology and definition are crucial, for the terms used in this protocol see S1 File Supporting Information.

## Materials and methods

### Study design

A transformative, mixed methods case study design will be used. This approach focuses on underrepresented or marginalised populations [32,^34^], such as children with learning disabilities and/or who are autistic and their families who will represent each case. It “investigates contemporary phenomena in depth and within its real-life context” ([35], p.18) in this instance children receiving cancer care and treatment.

The study will involve three consecutive phases (Fig 1). Phase one is quantitative in nature and will comprise an individual and organisational hospital survey, and a retrospective case note review. Phase two is qualitative in nature and will comprise ethnographic observations of patients’ and families’ cancer journey as well as interviews with families and healthcare professionals. Ethnography is a recognised methodology for facilitating prolonged observations of the patient journey and enabling understanding of what people actually do, as well as what they say about what they hear and remember [36–40]. Use of this methodology is recognised as “creating a more efficient, more effective, more equitable and more humane health care system” ([41], p.2223). Phase three will involve two workshops with families and health care professionals to review the study findings, identify innovative solutions for improving care and equity, and co-design resources for use in practice.

**Fig 1 pone.0333020.g001:**
[figure not shown]
Study overview.

### Public, patient involvement and stakeholder engagement

Public, patient involvement and stakeholder engagement are core to informing this study. We have established a parent advisory group (PAG) comprising eight parents whose children have previously received cancer care. These parents were drawn from existing hospital stakeholder groups, and further engagement with key stakeholder organisations, including the Down’s Syndrome Association and the Children & Young People Cancer Association (CCLG). The PAG will meet approximately three times per year, facilitated by the project coordinator and a clinical psychologist. In addition, a separate children and young persons’ advisory group has been made up, including children with and without learning disabilities and/or who are autistic. Both of these groups will support the study design development, including recruitment processes and participant facing materials.

### Setting

Children’s cancer care in the UK is delivered through a network of 21 tertiary centres, referred to as principal treatment centres [42] (PTC). The PTC retains overall responsibility for the cancer treatment plan, and for some PTCs defined aspects of care are delivered using a paediatric oncology shared care model, provided through Paediatric Oncology Shared Care Units [42] (POSCU). The phase 1 individual and organisational level survey will be conducted across the national network of PTCs and SCUs facilitated by the Children and Young people’s Cancer Association (CCLG). The retrospective case note review and phase two qualitative phase will be conducted primarily at one PTC, which partners in its care with another local site which will be involved as a secondary site. The service treats approximately 500 patients each year, accounting for approximately 28% of UK childhood cancer cases.

Phase 2 qualitative data collection will take place in a specialist children’s hospital on the cancer wards or outpatient settings, and other clinical areas relevant to delivery of cancer care.

## Methods and analysis

### Phase 1 quantitative

#### Hospital staff survey (1a).

A cross-sectional staff survey has been piloted and will be conducted across the UK in the first year of the project. It focuses on staff perceptions around their confidence to deliver equitable care for children with and without learning disabilities and/or who are autistic. The anonymised survey contains participant demographic questions, closed questions using mostly five-point Likert scales and free text questions. The survey will be distributed via the Children & Young People’s Cancer Association (CCLG) a national network and is open to all staff delivering cancer care in their role to children under 16 years. We will encourage those completing the survey to share with at least five colleagues across the multidisciplinary team, to create a snowballing sample. We estimate 500 responses will provide a robust data set with which to answer the research questions. Descriptive statistics will be used to characterise the sample. Composite variables will be computed to represent capability, capacity, confidence, safety and values separately for questions related to the two groups. Composite variables and individual questions, e.g., related to partnership working, environment, transition, parental burden and meeting needs, will be analysed using non-parametric statistics, comparing responses about children with learning disabilities or those who are autistic to those without. Comparison of responses from different professional groups and experience levels will be conducted using non-parametric statistics.

#### Organisational level survey (1b).

The organisational survey will be developed, piloted and distributed in year two of the project, following and informed by data collection and analysis from the individual healthcare professionals’ survey and early data collection and analysis from work package 2. The descriptive cross-sectional online survey will be anonymised and directed to clinical service level leads. The survey will map provision, policies and practices comprising a range of questions including focus around workforce, training, and service delivery models related to the delivery of cancer care to children with learning disabilities or who are autistic. Similar to work package 1b, the survey will be advertised through the CCLG network where organisational leads will be identified and made aware of the survey for completion. We estimate approximately 500 responses will provide a representative sample with sufficient scope to address the aims of this work package. The sample will be characterised using descriptive statistics. Composite variables and individual questions, e.g., related to provision, policies and practices will be analysed. Comparisons will be made between organisations using non-parametric statistics.

### Retrospective clinical case note review (1c)

The research team will work with the local digital data team to a) define the cohort specification, b) extract data according to pre-defined criteria such as patient demographics, co-morbidities, care episodes (e.g., length of stay, unplanned admissions), symptom profiles and treatment toxicity (e.g., pain, constipation, nausea and vomiting), and clinical outcomes (e.g., mortality, requirement for a bone marrow transplant, transfer to an end-of-life pathway).

The inclusion criteria will encompass children and young people who have received cancer care at the primary hospital research site between 1^st^ April 2019–31^st^ December 2023. This timeframe accounts for the implementation date of a new electronic patient record system within the hospital to the current time. A subsequent process will be undertaken to determine which of these patients have diagnoses of learning disabilities and/or ASD compared to those without. Within the digital environment, ICD-10 cancer related terms in oncology and haematology will be applied to establish the total case number. Against this case list, phrases relating to learning disabilities and ASD diagnoses will be applied to distinguish those cases with cancer and diagnoses of learning disabilities and/or ASD and those without. Data will be deidentified prior to analysis by the research team.

Data will cover standard structured clinical administrative data and free text clinical notes for all patients from the Electronic Patient Record (EPR) system. A data analyst will use Python and R to develop the pre-processing and exploratory data analysis code required in the initial pilot phase of the study. This analyst will develop a pipeline to wrangle the data into a format that is suitable for downstream analysis, including implementation of a text mining/search process and rule-based algorithm to identify and classify patients with and without learning disabilities and/or ASD diagnoses.

Statistical analysis will begin at a descriptive level to provide an overview of the different cohorts of children and young people with/without learning disabilities and/or ASD diagnoses. Further inferential statistics will be used to establish whether there are differences in outcomes associated with children having learning disabilities and/or ASD diagnoses using propensity score matching where appropriate, to reduce bias in the patient groups for comparison. The groups will be matched against a set of relevant factors. Resulting matched cohorts will be analysed to ascertain true differences between groups.

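### The article recognises that background and treatment symptoms overlap but does not separate them in the case note review, so an excess of recorded symptoms cannot by itself be read as more side effects

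*Protocol article*

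**What the plan says.** Under Phase 1 objectives, the protocol article hypothesises that children with learning disabilities and/or who are autistic "will have increased number and severity of side effects compared to children without learning disabilities and/or who are autistic and their families".

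The data for this come from Retrospective clinical case note review (1c). Among the items to be extracted from structured data and free-text notes are "symptom profiles and treatment toxicity (e.g., pain, constipation, nausea and vomiting", with one list of examples for both terms. Co-morbidities are extracted too, and the extraction criteria are said to be pre-defined.

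The last paragraph of that section names propensity score matching, where appropriate, on a set of relevant factors that it does not list. It says that analysis of the matched cohorts will establish true differences between groups.

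The Introduction bears on this in four places:

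- Autistic children have "physical manifestations which overlap with common cancer or cancer treatment-related symptoms such as pain, sleep disturbances and fatigue, gastrointestinal (GI) problems or immune dysregulation".
- It continues: "These symptoms can be exacerbated by cancer-directed therapy or be misinterpreted".
- Of children with learning disabilities it says: "They are almost twice as likely to report three or more health problems".
- In Down's Syndrome with leukaemia, "chemotherapy tends not to be tolerated very well with a greater risk of side effects, particularly serious infections".

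**The concern.** A side effect is something that treatment caused. A symptom in the record during treatment may have been caused by treatment, by the cancer, or by a condition the child already had. If the last of these is more common in one group, that group can show more recorded symptoms when treatment does the same to both.

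The Introduction identifies this overlap, but the description of the case note review does not carry it forward. Symptoms and toxicity are one domain, and matching is the only bias control described. Matching balances the covariates that enter the score. It does not make a recorded symptom mean the same thing in both groups unless each symptom's own pre-treatment status is measured and used.

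At stake is how the hypothesis test is read. An apparent excess of side effects could not be told apart from a difference present before the first treatment, and the two call for different responses in practice.

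**Working it through.** **No figure to reproduce.** The article gives no rate, significance level, power or group size for the case note review. Every input below is an assumption, chosen to show the mechanism.

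**Model.** Let *t* be the treatment-caused risk of a symptom, equal in both groups, and *b* the background prevalence. Then

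P(recorded) = 1 − (1 − *t*)(1 − *b*).

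**Main illustration.** *t* = 0.40; *b* = 0.30 in the learning disability/autism group and 0.10 in the other.

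- Learning disability/autism group: 1 − 0.60 × 0.70 = 0.58
- Other group: 1 − 0.60 × 0.90 = 0.46
- Odds ratio: (0.58/0.42) / (0.46/0.54) = 1.62

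The chance of a significant result (two-sided 5% normal test of two proportions) is about 47% with 120 per group.

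For an unmatched comparison of 120 versus 2,255 it is about 74%. The total of 2,375 is 500 patients a year (Setting) × 4.75 years (1 April 2019 to 31 December 2023). It would count children treated over several years more than once, so it is only a rough upper guide. The split is assumed.

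**Range of background prevalence in the learning disability/autism group** (10% in the other group, *t* = 0.40):

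| Background | Recorded | Odds ratio | Chance significant, 120 per group |
|---|---|---|---|
| 20% | 52% vs 46% | 1.27 | 15% |
| 30% | 58% vs 46% | 1.62 | 47% |
| 50% | 70% vs 46% | 2.74 | 97% |

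**Other values of *t*.** At 100 per group, with background of 20% / 30% / 40% versus 10%:

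- *t* = 0.30: odds ratios 1.34 / 1.77 / 2.35; chance of significance 17% / 51% / 85%.
- *t* = 0.50: odds ratios 1.23 / 1.52 / 1.91; chance of significance 11% / 30% / 59%.

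With equal background (10% versus 10%) the difference is zero and the chance of significance returns to 5%.

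**An opposing force.** Suppose all symptoms are recorded in the other group, but only a fraction *r* of those present in the learning disability/autism group. In the main illustration the excess disappears when *r* = 0.46/0.58 = 0.79, and reverses below that. The article gives no basis for choosing *r*.

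**Counting new onset: the denominator matters** (main illustration).

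- Among children free of the symptom before treatment: 40% versus 40%, odds ratio 1.0.
- Over all children: 0.70 × 0.40 = 28% versus 0.90 × 0.40 = 36%; odds ratio (0.28/0.72) / (0.36/0.64) = 0.69. This is bias in the opposite direction, because children who already have the symptom cannot acquire it.
- Adding worsened symptoms over all children restores 1.0 only if worsening is equally likely in the two groups (40% in each here).

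**The case against.** The strongest reply is that no sentence says background symptoms will be scored as side effects. Symptom profiles and treatment toxicity are two named items, the extraction criteria are pre-defined, and a journal article commonly leaves baseline windows, attribution and grading to the full protocol or analysis plan. Free-text notes could supply onset, and the unlisted matching factors could include baseline symptoms. All of this stands. A reader might infer that the plan counts long-standing symptoms as toxicity; the document does not support that. What remains is an inconsistency within the article: it recognises the overlap, describes the two items as one domain, and then describes matched differences as true ones.

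A reader might also infer that the bias favours the study's own hypothesis. The document does not settle this. The Introduction also mentions misinterpretation of symptoms, communication difficulty and diagnostic overshadowing, any of which could lead to under-recording. Two opposing biases of unknown size do not cancel by default; they make the result harder to read in either direction.

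The sources have limits too. The overlap sentence concerns autistic children and names pain and gastrointestinal problems, not constipation specifically. For learning disability the article gives only a greater general burden of health problems, not a higher rate of these symptoms. The Down's Syndrome text makes a real toxicity excess plausible, so an observed excess need not be artefact.

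**Conclusion.** The point holds as a limit on interpretation. As the article describes the data and the bias control, an excess of recorded symptoms in the learning disability/autism group would not by itself show more side effects, and matching on unspecified factors does not change that. The article does not show that the analysis will miscount symptoms, nor which way the net bias runs.

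The size is unknown. Under the assumed rates, equal toxicity yields odds ratios from 1.23 to 2.74, which shows that a modest background difference could matter. These are not estimates for this cohort. They rest on equal treatment-caused risk, independence of background and treatment symptoms, complete recording, and assumed group sizes. The point is worth acting on because the wording and outcome definition can be settled before the comparison is run.

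**What to change.** 1. Report symptom burden and treatment toxicity as separate outcomes.
2. Test the side-effect hypothesis on symptoms that are new after the first anti-cancer treatment, among children without that symptom in one common pre-treatment window, and on worsening among children who had it. Alternatively, adjust each symptom for its own pre-treatment status. State the denominator for each.
3. Report pre-treatment prevalence of each symptom by group as a descriptive result.
4. Reword the closing statement on true differences to say that matched comparisons show differences in recorded outcomes, subject to differences in background symptoms and in recording.

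**Cost.** One further time-stamped extraction from the same record, plus changes to the analysis wording.

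**Limits to state.** The pre-treatment window may be short and may include symptoms of the cancer itself. Children first treated before the April 2019 record system have no pre-treatment record in it and would leave this outcome only. The change does not correct under-recording in children who have difficulty communicating.
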